### Overview of Study Design

The primary study phases broadly consist of (1) prelaunch ethnographic observations, (2) iterative beta testing of the platform, and (3) a pilot trial. Throughout these phases, data will be collected to support the listed objectives via direct participant feedback (ie, electronic surveys, interviews and/or focus groups, and UCD sessions) as well as through observation of workflows and platform usage logs. Iterative platform refinements based on these data will be completed throughout each phase, with the implementation tool kit finalized at study conclusion. Each of these phases is described further under their respective headings below, with definitions of study activities provided in Textbox 1 and a planned timeline for study activities in Table 3.

Textbox 1.Study activities defined.Ethnography involves direct observation of users in their natural environment. We will use prelaunch and post-beta test and pilot ethnography to observe workflows and identify breakdowns and opportunities for technology refinement. [49]Stakeholder engagement includes focus groups or interviews using semistructured prompts modeled from RE-AIM (Reach, Effectiveness, Adoption, Implementation, and Maintenance) constructs and/or from ethnographic findings. We will use a variety of user-centered design strategies to engage end users to ascertain preferences, experiences, and priorities for using Peer PLUS (People Leveraging Urgent Support), including barriers and facilitators. Findings will inform updates to the platform and implementation tool kit.Surveys will be used to capture various measures of usability, user experience, and impact on recovery, client-PRC (peer recovery coach) alliance, and health outcomes, as well as participant demographics, and are detailed in Textbox 2.Semistructured interviews will focus on 2 critical components for predicting adoption of new technologies: perceived usefulness and relative advantage. [50] As our PRCs already use technology for both communication and tracking, the perceived usefulness and relative advantage of Peer PLUS for each of these uses will be explored.PRC client tracking sheet is a spreadsheet currently used by PRCs to track certain client data as part of standard practice. We will leverage this to gather demographic data related to this overall client population and characterize nonparticipating clients.Peer PLUS use log data will be collected automatically by the app. Data points include (1) user-specific logins, (2) number and type of messages sent (eg, standard, appointment, and referral), (3) number of resources viewed and uploaded, (4) number of calendar appointments added, (5) number of client profile edits, (6) time elapsed between message received and read, and (7) time elapsed between notification sent and app opened. We will not collect message content, names, or other personal identifiers; data stored and analyzed will use participant ID numbers, and dates will be represented as time elapsed since study initiation.Implementation tool kit development includes definitions, policies, and procedures for both setup and usage of the platform. This will be developed iteratively throughout the study using findings from all phases.

Textbox 2.Inclusion and exclusion criteria.
**All participants: inclusion criteria**
Aged 18 years or olderLives in the United StatesReads, speaks, and understands EnglishAgrees to voice and video recording during interviews and/or focus groupsConsents to participate in the study
**Client: inclusion criteria**
Has a substance use disorder (SUD) diagnosisReceives SUD support from a peer recovery coach (PRC)Has access to a functioning Android or Apple smartphone with the ability to receive and send textsFor clients with Android smartphones only, must have a Gmail account or be willing to set up a Gmail accountAble to download apps from their smartphone’s app storeHas an accessible email address or is willing to set up an email accountPer PRC’s professional judgment, is an appropriate candidate to participate in the study
**Client: exclusion criteria (pilot only)**
Has been engaged in the program for more than 6 months
**PRC: inclusion criteria**
Employed as a PRCUses an Android or Apple smartphone as part of their PRC dutiesFor PRCs with Android smartphones only, they must have a Gmail account or be willing to set up a Gmail accountAble to download apps from the smartphone’s app store
**PRC manager: inclusion criteria**
Employed as a PRC manager or supervisor

**Table 3. T3:** Breakdown of the activities as it relates to the initial timeline.

Months	Activities
0‐3	Prelaunch ethnography
4‐8	Beta testing
9‐12	Platform and tool kit refinement
13‐20	Pilot
21‐22	Platform and tool kit refinement
23‐24	Final analysis and Go/No Go R33

The beta tests and pilot will involve app usage by clients and PRC participants as part of their existing support relationship and in addition to standard care, with PRCs additionally using the platform’s client management system. All client participants will be clients of a PRC who is also enrolled in the study, and each PRC participant may have multiple clients enrolled. Participants will be asked to use the app for asynchronous communication outside of in-person meetings, when possible. The length of participant engagement for a beta test or pilot trial was planned to last up to 3 or 6 months, respectively.

During and immediately after their trial period, participants’ perceptions and experiences will be assessed through periodic deployment of electronic surveys along with posttest engagement. During beta testing, these surveys will be focused primarily on the usability of the platform; during the pilot, clients will be additionally surveyed regarding certain treatment outcomes. Descriptions of survey measures are listed in Textbox 3. Further, after each phase, additional user observations, interviews and/or focus groups, and UCD sessions will be conducted. Feedback from participants throughout all phases, in addition to application usage logs, will be used to iteratively refine the app and contribute to the development of a finalized implementation tool kit at study completion (Table 4). Any updates to software functionality or improvement opportunities identified during the beta testing and pilot phases will be implemented and tested by our development and user experience team until the app is stabilized.

Textbox 3.Survey instruments.System Usability Scale (SUS) [44] is a 10-item validated instrument for measuring usability of a variety of products, including software. Scores range from 0 to 100. A score above 68 is considered above average.Substance Use Recovery Evaluator (SURE) [45] is a 21-question psychometrically valid instrument measuring recovery from drug and alcohol dependence. Respondents use a 5-point response set to indicate frequency of use and cravings, self-care, material resources, outlook on life, and relationships. Each item is scored as 1‐3 and scores are summed. A higher score indicates greater recovery.CAHPS Experience of Care and Health Outcomes (ECHO) [48] is a 37-question instrument that has been validated to assess an individual’s experience with behavioral health care and services. We will use the 6-item Communication Quality subscale to evaluate the clients’ experience with peer recovery support, replacing the word “Clinicians” with “Peer Coach*.”*Working Alliance Inventory (WAI-SR) [46,47] is a 12-item survey that will be used with both client and PRC participants to assess 3 aspects of therapeutic alliance: (1) agreement on tasks of therapy, (2) agreement on goals of therapy, and (3) development of an affective bond. “Recovery” will replace “therapy” to align with the study setting, as PRCs do not provide therapy but rather provide support during recovery.Custom user experience (UX) survey questions will be shaped by stakeholder engagements and will incorporate RE-AIM (Reach, Effectiveness, Adoption, Implementation, and Maintenance) elements [38] and the technology acceptance model frameworks adapted for health care [51].Demographics will be collected through a custom survey at the time of enrollment.

**Table 4. T4:** Study data points. Data points collected for research operations are not included.

Participant types and study data points	Applies to		Source
	Beta tests	Pilot	
All client participants			
Demographic data	✓	✓	Enrollment survey
WAI-SR^a^		✓	Postenrollment surveys
SUS^b^ and/or Custom UX^c^	✓	✓	Postenrollment surveys
SURE^d^ and ECHO^e^		✓	Postenrollment surveys
Peer PLUS^f^ use data	✓	✓	Application server
All or select client participants			
Data from stakeholder engagements	✓	✓	Posttest UCD^g^ activities
All PRC^h^ participants			
Demographic data	✓	✓	Enrollment survey
WAI-SR		✓	Postenrollment surveys
SUS and/or Custom UX	✓	✓	Postenrollment surveys
Peer PLUS use data	✓	✓	Application server
All or select PRC and PRC manager participants			
Data from stakeholder engagements	✓	✓	Posttest UCD activities
Data from prelaunch ethnography	✓		Prelaunch ethnography
Data from post-beta test and pilot ethnography	✓	✓	Posttest ethnography
Data from post-beta test and pilot semistructured interviews	✓	✓	Posttest interviews
Study-wide (not participant-specific)			
Nonidentifying data: clients not asked to participate, for example, race, ethnicity, and age group		✓	PRC client tracking sheet
Nonidentifying data: clients declining to participate, for example, race, ethnicity, age group, and reason for declining (collected as general qualitative feedback)	✓	✓	Screen failure log

a WAI-SR: Working Alliance Inventory.

b SUS: System Usability Scale.

c UX: user experience.

d SURE: Substance Use Recovery Evaluator.

e ECHO: Experience of Care and Health Outcomes.

f PLUS: People Leveraging Urgent Support.

g UCD: user-centered design.

h PRC: peer recovery coach.

Study activities involving direct interaction with participants (eg, informed consent meetings, observations, interviews, and UCD activities) will generally take place at a health system facility or via videoconferencing, but could also occur in a private community-based setting. Surveys will be deployed virtually using REDCap, a HIPAA-compliant web-based survey platform, and distributed via text, email, and/or Peer PLUS. Client participants will complete surveys on their personal devices, and PRC and manager participants will complete them during work hours on the device they use for work.

### Prelaunch Rapid Ethnography

Prior to user testing, we planned to conduct a prelaunch rapid ethnography [52] of up to 4 PRCs to document workflows and process requirements that may be altered with the integration of the platform, including direct interaction with clients, caseload management, resource sharing, and report generation. Through these observations, we sought to understand opportunities for improved productivity and client connection, including day-to-day work that is not quantified in existing workflow documentation. This served as the initial foundation for the development of implementation tool kit components.

Several months prior to beta testing, the study team observed 3 PRCs who represented the different types of coaches within our specific program—maternal, community, and emergency department—over a period of approximately 8 hours each. PRCs were identified by their manager as they represented the different types of coaches. The research team reached out to PRCs to assess their interest in participating and obtained verbal agreement to participate. At the beginning of each observation, the researchers explained the procedure and made sure that any questions they might have were answered. Observations were recorded through detailed written notes with time stamps and descriptions. During these observation sessions, paper-based documents containing resources that may be provided to clients were reviewed and copied in preparation for integration into the Peer PLUS platform. To validate and inform the translation of these ethnographic findings into the development of the platform, we subsequently engaged in follow-up discussions with PRCs and managers to provide clarity regarding our observations in a series of co-design sessions. In particular, we collated resources that were collected during these observations and met with 3 PRCs to discuss how to optimally organize and present them in the mobile app. Once the initial version of the app was finalized, we began recruitment for beta testing.

### Beta Testing and Pilot Trial

#### Sample Size and Planned Recruitment Rate

We planned to conduct up to 3 incremental beta tests of Peer PLUS, with up to 4 PRCs and up to 4 clients per PRC (n=16 clients) per test. After beta testing is completed, up to 15 PRCs and up to 40 clients will pilot Peer PLUS, which is in line with HCI testing practices [53]. After each test phase, select clients and PRCs will participate in stakeholder engagements to reflect on their experiences. The PRC manager will be involved throughout all phases of the study; in the context of our existing collaborative relationship, the manager has provided design input and serves as an intermediary between the research team and PRCs rather than being enrolled as a consented participant. However, the protocol was written to allow for manager participants (eg, in the case of changes to staffing or location). In total, up to 4 PRC managers, 16 PRCs, and 88 clients may participate across both phases; refer to Table 5.

**Table 5. T5:** Maximum number of participants per study activity.

	Peer PLUS^a^ use	Stakeholder engagements	Surveys		
			WAI-SR^b^	SUS^c^ and/or Custom UX^d^	SURE^e^ and ECHO^f^
Each beta test					
Clients	16	8	—^g^	16	—
PRCs^h^	4	4	—	4	—
PRC managers or supervisors	4	4	—	4	—
Pilot					
Clients	40	8	40	40	40
PRCs	15	15	15	15	—
PRC managers/ or supervisors	4	4	—	4	—

a PLUS: People Leveraging Urgent Support.

b WAI-SR: Working Alliance Inventory.

c SUS: System Usability Scale.

d UX: user experience.

e SURE: Substance Use Recovery Evaluator.

f ECHO: Experience of Care and Health Outcomes.

g Not applicable.

h PRC: peer recovery coach.

#### Eligibility Criteria

Study participants were included based on the criteria listed in Textbox 2. In this study, PRCs were employed by the health system of the study, although their clients may not be patients of that health system, as they may have been referred through another pathway. This participant population is appropriate for the subject of study due to their status as intended real-world users of the mobile app engaged in a peer support relationship. For the pilot test in particular, we updated the criteria to exclude clients who had been engaged in the peer recovery program for more than 6 months, based on feedback from initial beta test participants regarding the specific utility of the Peer PLUS platform in building the PRC-client relationship and introducing new resources during the early stages of treatment.

#### Screening, Recruitment, and Enrollment

Screening for participant recruitment will occur in multiple steps. In each testing phase, PRCs will be contacted prior to clients. Once each PRC has agreed to participate, they will provide information for qualifying clients for the research team to contact, based on their knowledge of the recruitment criteria in relation to their client population. The research team will confirm that participants meet the criteria during this initial contact.

### Recruitment Methods

#### Beta Testing Phase

During beta testing, engagement is key to success; as such, we sought to enroll participants who would be particularly interested and invested in helping evaluate and identify problems in platform design and/or processes. To enroll PRCs, the study team asked the PRC manager to recommend PRCs they believed would fit this description. Once enrolled, PRCs then recommended clients. In each case, after receiving these recommendations, the study team contacted potential participants to assess interest and set up an initial meeting.

#### Pilot Phase

In the pilot phase, we will seek to enroll PRCs in a more naturalistic manner. As such, the study team will obtain a list of all currently employed PRCs from the manager and contact them to assess interest. Once enrolled, their clients will form the pool of eligible participants. The trust between the PRC and the client is key. Thus, a purely naturalistic recruitment strategy for clients is not feasible, as we wanted to ensure that trust in the program had been developed before approaching newer clients to participate in the study, and we did not want to disrupt the health system’s existing processes for engaging clients in the program. The study team will provide recruitment flyers and training on inclusion and exclusion criteria to PRCs so that they can introduce the study to their clients. If an eligible client expresses interest, the PRC will check “Yes” in the “informed about study” section in the client management system. The study team will run reports to identify which clients have been informed about the study and thus need to be contacted for recruitment. For all recruitment activities, participants may be initially contacted by phone and/or email (and/or Microsoft Teams, in the case of PRCs). Institutional review board (IRB)–approved scripts for emails and calls will be used but may be adapted as necessary for clarity and/or to answer participant questions or concerns.

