## Methods

### Feasibility Objectives and Outcome Measures

This work constitutes the first phase (R21; 2 years) of a 5-year federal research grant from the Agency for Healthcare Research and Quality (AHRQ) to test Peer PLUS, develop an implementation tool kit, and determine whether the tool has sufficient usability and impact to move to the final phase of the grant (R33; randomized clinical trial). The study aims and associated objectives and outcome measures for the present phase are summarized in Table 2.

To accomplish these objectives, in year 1, we will conduct a series of UCD activities, refine the platform, and deploy it with a small sample during beta testing. In year 2, we will continue UCD work, complete further refinement, develop an implementation tool kit, and conduct a pilot study.

For aim 1, we will use UCD methods to refine the functionality of Peer PLUS (eg, develop new features) and apply implementation science frameworks to develop an implementation tool kit. We will validate usability with the 10-item System Usability Scale (SUS) [44] and our own custom user experience survey incorporating RE-AIM elements. We will also measure frequency of use through app interaction logs as a proxy to determine likelihood of sustained use in the proposed R33 phase. Primary outcome measures for the pilot study will include usability ratings (SUS score ≥68; ie, above average) and app usage statistics (20% more connections to clients using the app, compared to contacts with nonparticipating clients, which is documented as standard of care). Based on the client population of the health system, we will target 25% as the proportion of clients approached who are eligible and consent to determine the feasibility of recruiting the target sample size (n=200) for the trial proposed in the R33 phase.

In aim 2, we will assess the platform’s impact on clients through several validated instruments, including the Substance Use Recovery Evaluator (SURE) [45] to assess recovery, the Consumer Assessment of Healthcare Providers and Systems (CAHPS) Experience of Care and Health Outcomes (ECHO) [48] to assess experience with receiving PRC services, and the WAI-SR [46,47] to assess therapeutic alliance. This will demonstrate the ability to robustly evaluate the app in the proposed R33 trial.

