### Ethical Considerations

The study protocol and all applicable documents and amendments were approved by the Parkview Health Institutional Review Board (PRC21-0707 PLUS). The minimal risks associated with participation are outlined in the consent form, which all participants will electronically sign prior to participation in a beta test or pilot during the informed consent process detailed in the “Consent” section above. IRB-approved scripts will be used during recruitment and consent processes to describe study procedures, rights as research participants, and compensation. Participants will be compensated between US $15 and US $25 per study engagement, as approved by the IRB and described further in the “Participant Incentives” section above. Due to the sensitive nature of health data and the vulnerable population included in this study, measures will be taken to protect participants’ privacy and confidentiality, including storing data securely, coding participant data with unique identifiers stored separately from a password-protected code key, and encrypting exchanges of data between participant devices and the server to prevent unauthorized interception. The client management system is not available for download and follows data safety protocols as established by the health system. The mobile app will undergo extensive penetration testing by a third party to identify any security issues prior to the pilot launch. Issues identified will be addressed prior to PRC and client use of the app. During the study, access to the Peer PLUS mobile app will be restricted to participants and the research team; researchers will not review messages exchanged by participants. If a participant leaves the study for any reason, their access to Peer PLUS will be removed. If a PRC withdraws, their clients will be offered the option to either withdraw or be reassigned to another participating PRC, who will have access to all information visible to their previous PRC. Any data or findings shared outside of the research team will be deidentified and/or aggregated. Additional measures to protect participant safety are detailed under “Safety Protocols” below.

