### Statistical Analysis Plan

Data will be analyzed at the aggregate level. To address aim 1 (usability and potential for sustained use), descriptive statistics will be computed on the SUS and recruitment rates to assess whether feasibility targets are met (ie, SUS score ≥68, 25% client eligibility and recruitment rate). Using data collected from the Peer PLUS user log, we will conduct a general categorical analysis as a proxy for end-user engagement. To assess our primary outcome related to client contact, in the pilot trial, we will compare the number and rate of connections to clients using the platform to PRCs’ documentation of contact with nonparticipating clients to determine whether the target of 20% more contacts with enrolled clients was met. Further, to address aim 2 (evaluating the impact of Peer PLUS on treatment-related outcomes), descriptive statistics will be calculated for the SURE, CAHPS ECHO, and WAI-SR survey measures deployed during the pilot trial, which will demonstrate potential improvement related to recovery, quality of care, and therapeutic alliance, as well as the feasibility of using these measures to evaluate the app in the R33 phase.

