This project was proposed due to the limited understanding of the impact of technology-facilitated communication between PRCs and their clients. The unique role of the PRC as nonclinical staff who provide support to clients in a manner that is both formal (ie, as employees of a health system, with a need to document and track various data for operational and reporting purposes in a manner that is compliant with legal regulations and company policies) and informal (ie, as peers, with communication often occurring through personal devices) presents many challenges to both communication and documenting client engagements. Prior to study initiation, our health system’s PRCs relied on face-to-face meetings, text messaging, paper mail, and voice calls to communicate with hundreds of existing and potential clients per month, a system that is inefficient and limits topics of discussion due to privacy and security concerns. Moreover, tracking these interactions was done manually, which is prone to errors and disrupts workflow, displacing time that could be spent engaging in meaningful client interaction. A system that offers secure communication that can be tracked with background analytics is a solution to this problem. As engagement with community resources and treatment providers is an additional goal of client support, a digital solution to track referrals and completion of activities will also help to elucidate the most used and helpful nodes in the ecosystem of support surrounding clients.

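### The primary 20% contact target compares clients selected on engagement with nonparticipants on whom no engagement condition is stated, so selection alone could push the rate ratio above 1

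*Protocol article*

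**What the plan says.** All references are to the protocol article.

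- **The target.** Feasibility Objectives and Outcome Measures makes this a primary pilot outcome: "20% more connections to clients using the app, compared to contacts with nonparticipating clients, which is documented as standard of care". Table 2 lists it as a milestone, and the timeline in Table 3 ends in a Go/No Go decision for the R33 phase.
- **The analysis.** The Statistical Analysis Plan section says "we will compare the number and rate of connections to clients using the platform" and sets these against PRCs' "documentation of contact with nonparticipating clients to determine whether the target of 20% more contacts with enrolled clients was met".
- **Entry to the enrolled group.** Under Recruitment Methods, Pilot Phase, the reason for not recruiting clients purely naturalistically is that "we wanted to ensure that trust in the program had been developed before approaching newer clients to participate in the study". The next step applies "If an eligible client expresses interest". The client inclusion criteria add that, in the PRC's professional judgment, the client "is an appropriate candidate to participate in the study". Clients more than 6 months into the program are excluded from the pilot.
- **The comparator.** It is named only as nonparticipating clients. Table 4 has a pilot row, drawn from the PRC tracking sheet, for clients who were never invited, and Textbox 1 says that sheet will be used to describe nonparticipants.

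**The concern.** A client who drifts away early is unlikely to be approached, voice interest, be put forward by the PRC and attend a consent meeting. That client remains a nonparticipant. The filters for enrolment are therefore also filters for being in contact with the PRC, and the comparison group has no equivalent filter.

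This differs from a mismatch in eligibility. Restricting comparators to clients within the 6-month limit would not remove it: an otherwise eligible client who went silent in week 3 would still add low-contact time to one group only.

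The target feeds a decision about a randomized trial. If selection can yield a 20% excess by itself, meeting the target says little about whether the app increases contact. The Limitations section does not mention this selection.

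**Working it through.** **Inputs from the article.** Target ratio 1.20; pilot use of up to 6 months; up to 40 enrolled clients. The 20% is a chosen threshold with no derivation behind it, so there is no calculation of the plan's to reproduce.

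**Inputs not in the article (assumed).**
- d: share of counted nonparticipant time that is disengaged.
- r: contact rate in that time relative to engaged time.
- e: share of counted enrolled time that is disengaged.
- No app effect, and equal contact rates while engaged.

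**Step 1: enrolled time fully engaged (e = 0).**

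Ratio = 1 / (1 − d(1 − r)).

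With r = 0:

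| d | Ratio |
|---|---|
| 5% | 1.05 |
| 10% | 1.11 |
| 20% | 1.25 |
| 30% | 1.43 |

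**Step 2: where the ratio reaches 1.20.**

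d = (1 − 1/1.2) / (1 − r) = 0.1667 / (1 − r).

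- r = 0: 16.7%
- r = 0.25: 0.1667 / 0.75 = 22.2%
- r = 0.5: 0.1667 / 0.5 = 33.3%

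**Step 3: some enrolled time also disengaged (contact-free in both groups).**

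Ratio = (1 − e) / (1 − d), so d = 1 − (1 − e)/1.2. With e = 10%, d = 1 − 0.90/1.2 = 25%. With e = 20%, d = 33.3%. If e = d, the ratio is 1.00 and the effect disappears.

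**Step 4: in terms of clients who drop away.** Assume a constant rate of disengagement over 6 months and let x be the cumulative hazard. The engaged share of time is (1 − exp(−x))/x. Setting this to 1/1.2 gives x = 0.376, so 1 − exp(−0.376) = 31% of nonparticipants disengaged by month 6. Other values, with e = 0 and r = 0:

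| Disengaged by month 6 | Rate ratio |
|---|---|
| 10% | 1.05 |
| 20% | 1.12 |
| 30% | 1.19 |
| 40% | 1.28 |
| 50% | 1.39 |

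**Step 5: chance of meeting the target with no effect.** A simulation used 40 enrolled clients, with an assumed 100 nonparticipants, 4 contacts per month while engaged and client-to-client variation (gamma shape 1 to 4). The observed ratio was at least 1.20 in 3–16% of runs with no disengagement, 46–48% at 30% disengaged by month 6, and 62–72% at 40%.

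**Step 6: raw number instead of rate.** The plan names both number and rate and does not say which decides. If enrolled clients lose 1 of 6 months while trust forms and then stay engaged, the ratio of contacts per client is 5/6 of the rate ratio: (5/6) × 1.189 = 0.99 at 30% disengagement and (5/6) × 1.386 = 1.16 at 50%. Neither reaches 1.20.

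**The case against.** **The article does not give the counting rules.** A reader might infer that enrolled contacts are counted only from the time trust has formed until the client leaves the study. The sentence "If a participant leaves the study for any reason, their access to Peer PLUS will be removed" does not establish that. It is an access rule under Ethical Considerations and does not concern counting. Leaving the study is also not the same as disengaging: an enrolled client who goes quiet without withdrawing may still be counted. This part of the objection stands, and the point rests on entry alone.

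**The comparator is not shown to contain disengaged or prospective clients.** A reader might take "communicate with hundreds of existing and potential clients per month" to mean that prospective clients are in the denominator. That sentence describes workload before the study and defines no comparator. Nonparticipants also include clients who declined, and these were reachable when approached. This stands too. What remains is that never-invited clients are among nonparticipants and that no activity condition is stated.

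**It is not immortal-time bias.** That label would require guaranteed pre-enrolment time to be credited to the enrolled group, and nothing in the article does so. The accurate term is selection on engagement.

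**The direction is not certain.** Step 6 shows that on raw number a shorter enrolled window works against the target. If early program weeks are contact-heavy, comparators who include them would also gain. Both are fair.

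**An article leaves such details to the full protocol or analysis plan.** For the counting window and denominator this is right, and their absence is not the criticism. The comparison itself is stated in two places, as is the selective entry, and the two together create the problem.

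**Conclusion.** The concern holds as a weakness in the stated comparison. Enrolled clients are selected on formed trust, expressed interest and PRC judgment, while nonparticipants carry no stated condition on engagement or time in program. As written, the plan permits a rate ratio above 1 with no app effect.

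The size is conditional. With enrolled time fully engaged and equal contact rates while engaged, 1.20 is reached at about 17% disengaged nonparticipant time with no contacts. That rises to 22% or 33% if contacts continue at 25% or 50% of the usual rate, and to 25% if a tenth of enrolled time is also disengaged. The article gives none of these shares, so the figures show what moderate disengagement could do and do not estimate what it will do.

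The documents do not support the stronger reading that the target will be met through survivorship. The change should be made before the Go/No Go decision.

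**What to change.** Base the 20% verdict on one rate ratio, defined before the pilot data are examined:

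1. Count PRC-documented contacts through all channels, from the same source for both groups.
2. Take each enrolled client's enrolment date as the index date. Compare with nonparticipants of the same PRC who, on that date, are within the 6-month program limit, at a similar time in program, and have a recent documented contact (for example, in the previous 30 days).
3. Count both groups from the index date to the same fixed day (for example, day 90). Keep enrolled clients in the count after they stop using the app or go quiet, as far as consent allows.
4. State that selection by interest and PRC judgment remains even so, and that meeting the target is not by itself evidence of an app effect.

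**Cost.** Extra extraction and analysis work on coded client-level contact records. The client management system is already in use across the PRC team, and the plan already intends to use contact documentation for nonparticipants. However, Table 4 lists only nonidentifying characteristics for clients who were never invited, so an ethics confirmation may be needed for their dated contact records. The ratio will probably look less favourable. Recruitment and care do not change.
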